The sample size is based on both the number of healthcare organizations and the number of healthcare personnel in each organization. We aim to accumulate data on a minimum of 150 healthcare personnel per cluster over 2 years. Thus, if an organization is in the trial for two years they will have to contribute at least 300 healthcare personnel to the trial. Note that we define a cluster as a healthcare organization. Sample size was calculated based on the equations of Kelsey et al. for Randomized Clinical Trial Studies (18) and multiplied by the design effect to get the number of subjects required for the cluster design. The level of difference between intervention organizations and the control organizations set in determining the sample size was 20%. This requires randomization and evaluation of immunization campaigns in 46 healthcare organizations (clusters) with 6000 healthcare personnel. Twenty-three will be randomized to the intervention group. With an intra-cluster correlation coefficient set at 0.05 and an average cluster size of 150 eligible healthcare personnel per healthcare organization, we will need a total of 46 clusters for 80% power and 5% significance.

- 1. Statistical Methods

As outlined in the sample size calculation for the study, the statistical analysis will be based on analyses using cluster analytic techniques.

- 1. Interim Analysis and Stopping Rules

We will conduct an interim analysis after completion of Year One. There are no stopping rules.

1. **Randomization**
   1. Randomization Sequence Generation

After organizations have declared their willingness to participate in the study, they will be randomized to be in the Intervention Group or Control Group. Due to the relatively small number of healthcare organizations in the trial, minimization will be used to allocate participants to intervention and control to ensure maximum balance. After all participants have been recruited, organizations will be individually allocated to an intervention and/or control group by the Ottawa coordinating centre using computer-generated random number tables, embedded in a computer program for minimization. The variables to be used in the minimization process will be trial centre (Ontario and Manitoba) and healthcare organization size (small, medium, large).

Organizations assigned to the control group will be informed that they will have access to the Guide at the completion of the study.

- 1. Randomization Type

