Randomization will be performed using complete simple randomization.

1. **Statistical Methods**

The primary analysis will consist of comparing the Intervention Group with the Control Group. Characteristics of healthcare organizations will be compared descriptively at baseline. In order to adjust for the cluster design, we will calculate mean immunization rates and mean proportions of other characteristics for each healthcare organization to produce summary statistics.

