8.1 Primary Outcome

For Year One and Year Two, we will calculate the mean difference in immunization rates between the intervention year and baseline for both comparison groups. Assuming that the mean values are normally distributed within each group, we will use t-test to compare immunization rate difference means of the control group to the intervention group. We will consider *P* values < 0.05 to be significant.

Linear regression models will be used for continuous outcome variables (improvement in healthcare personnel immunization rates from the base year) and logistic models for binary outcome variables (attainment of the benchmark of 90% immunization rate set by the National Advisory Committee on Immunization). The assumptions for using each regression model will be checked and analyses adjusted accordingly. All analyses will be undertaken, adjusted for healthcare organization size, and for baseline variables which differ to a statistically significant extent between groups. Differential effects of the intervention by characteristics of healthcare organization and baseline rates will be assessed for the primary outcome measures by adding terms for the interaction between these characteristics and baseline rates and Intervention Group to the regression models.

Multilevel models will be applied to take account of clustering at the healthcare organization level and the Guide effects which will apply to differing extents in the intervention group (due to the effectiveness of campaigns in each participating healthcare organization). While the primary outcome will be attainment of the recommended benchmark of 90% set by the National Advisory Committee on Immunization, we will investigate the profile of immunization rate attainment at Baseline (2008-2009), Year One (2010-2011) and Year Two (2011-2012). This will be a repeated measures analysis. That is, evidence for differences in effect of the intervention at the different time points will be assessed.

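### Covariates are picked by baseline significance tests and trial centre, a minimization factor, is not fixed in the model: the model is left to chance and, if minimization governs and centre is prognostic, the test is conservative

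*Protocol*

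**What the plan says.** The covariate rule is in Protocol section 8.1 (Primary Outcome). All analyses are to be "adjusted for healthcare organization size, and for baseline variables which differ to a statistically significant extent between groups". Organization size is therefore always in the model; anything else enters only by passing a baseline test.

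Three other statements bear on this:

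- **Allocation.** Under Randomization Sequence Generation, "minimization will be used to allocate participants to intervention and control to ensure maximum balance", and two factors are named: "The variables to be used in the minimization process will be trial centre (Ontario and Manitoba) and healthcare organization size (small, medium, large"). The next subsection, Randomization Type, says: "Randomization will be performed using complete simple randomization".
- **Baseline comparison.** The opening of the main Statistical Methods section says: "Characteristics of healthcare organizations will be compared descriptively at baseline".
- **Headline test.** Section 8.1 first says "we will use t-test to compare immunization rate difference means of the control group to the intervention group". No covariates are named for that test, although the same section says all analyses are adjusted.

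Section 8 nowhere names trial centre as a covariate.

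**The concern.** There are two separate problems.

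**Selection by significance test.** In a properly randomized trial, a significant baseline difference is a chance event. It says nothing about how strongly the variable predicts the change in immunization rate. A rule that admits variables on this ground will usually leave out strong predictors and sometimes admit irrelevant ones. The model behind the reported estimate cannot be known until the data are seen. The rule also requires formal baseline testing, whereas the Statistical Methods section describes the baseline comparison as descriptive.

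**A balanced factor left out.** When allocation is forced to balance on a factor that predicts outcome, the treatment estimate becomes more precise. A model without that factor does not see the gain and reports a standard error that is too large. Under the stated rule, centre can enter only by differing significantly between arms, which minimization works to prevent.

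At stake are a pre-specified primary model and some power, in a trial of 46 clusters planned at only 80% power.

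**Working it through.** **Inputs from the protocol (Sample Size section).** There are 46 clusters, 23 of them in the intervention arm, with 80% power and 5% significance; I take the test as two-sided, which the protocol does not state. The covariate rule itself rests on no stated figure, so there is none to reproduce.

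**Inputs assumed.** The protocol does not say how much of the variance in change centre explains. I use R² = 0, 0.10, 0.20 and 0.30.

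**Step 1: chance of a data-driven model.** With k independent baseline variables each tested at 5%, the chance that at least one enters is 1 − 0.95^k:

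- k = 3: 14%
- k = 5: 23%
- k = 10: 40%

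Any single variable not used in the allocation, such as the 2008-2009 rate, enters in about 5% of trials and is omitted in about 95%, however prognostic it is.

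**Step 2: can centre enter?** Trials of 46 clusters were simulated with minimization on centre and three-level size (biased coin 0.8). Centre passed a 5% test in 0 of 15,000. With unstratified 23:23 allocation it passed in about 7% to 8%.

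**Step 3: effect of omitting centre when it is balanced.** The true standard deviation of the estimate shrinks by √(1 − R²), but the unadjusted model's standard error does not. In the normal approximation, with 1.96 + 0.842 = 2.802 for 80% power when R² = 0:

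- type I error, unadjusted = 2 × [1 − Φ(1.96 / √(1 − R²))]
- power, unadjusted = Φ(0.842 / √(1 − R²))
- power, adjusted = Φ(2.802 / √(1 − R²) − 1.96)

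For R² = 0.20, √0.80 = 0.894. Type I error is 2 × [1 − Φ(2.191)] = 2.8%. Unadjusted power is Φ(0.941) = 83% and adjusted power is Φ(1.173) = 88%.

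Simulation with the t distribution (40,000 runs, 46 clusters balanced within centre, no size term) gives nearly the same:

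| Centre share of variance | Type I, unadjusted | Type I, adjusted | Power, unadjusted | Power, adjusted |
|---|---|---|---|---|
| 0% | 5.1% | about 5% | 80% | 80% |
| 10% | 3.9% | about 5% | 81% | 84% |
| 20% | 2.9% | about 5% | 82% | 88% |
| 30% | 1.9% | about 5% | 84% | 92% |

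**Step 4: the protocol's own rule.** A further simulation applied minimization with size always in the model and other variables selected by significance. It used 2,500 runs per setting and assumed that size explains 10% of the variance and that one of five other variables explains 20%.

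- Type I error was 4.7%, 3.7% and 1.8% at centre shares of 0%, 10% and 30%.
- Mean standard error against true standard deviation was 0.283 against 0.263 at 10% (about 8% too large) and 0.285 against 0.241 at 30% (about 18% too large).
- At a 0.85 SD effect, power at 0%, 10% and 30% was 83%, 85% and 88%, against 83%, 88% and 95% with size and centre fixed in advance.

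**Step 5: unstratified allocation instead.** The size-only model was calibrated (type I error 4.6% to 5.4%), so the mismatch from omitting centre disappears. The significance rule remained data-driven and somewhat conservative (3.5% to 4.3%).

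**The case against.** The strongest reply is that the standard-error argument depends on two things the protocol does not settle. It needs minimization to govern, and the protocol also states simple randomization. It needs centre to predict *change*: the outcome is a difference from baseline, so stable level differences between centres cancel. Both points stand, and the standard-error part is conditional on them.

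Baseline rate is also not ignored. The outcome is change from it, interactions with it are to be added to the regression models, and a repeated-measures analysis includes the baseline year. This stands too. The 95% figure concerns only the baseline rate as a main-effect covariate under the selection rule.

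It is also unclear whether the covariate rule reaches the headline P value, because the t-test names no covariates. That is a reason to state the primary model plainly; it does not rescue the rule.

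One could say that covariates belong in the statistical analysis plan. But the protocol does not leave them open. It fixes a rule, and a plan that follows it inherits the defect.

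A reader might infer more than the documents support:

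- *That the standard errors are wrong as a matter of fact.* They are not if simple randomization governs or centre is not prognostic.
- *That centre can never enter.* It almost never would under minimization; under simple randomization it could by chance.
- *That power stays at 80% when a balanced factor is omitted.* It rises slightly, because the estimate's true variance still falls, so the loss is smaller than a comparison with 80% suggests.
- *That false positives are inflated.* Neither simulation shows this for the protocol's rule or for omission of centre.

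**Conclusion.** The criticism of covariate selection by baseline significance holds without condition on the allocation method. Its size is about a 23% chance that at least one of five independent variables enters, with the 2008-2009 rate omitted as a main effect about 95% of the time. It also conflicts with the protocol's descriptive baseline comparison.

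The omission of centre as a fixed covariate is a textual fact. Its consequence is conditional: if minimization governs and centre predicts change, the test is conservative and loses about 3, 6 or 8 points of power at centre shares of 10%, 20% or 30%. With no centre effect, nothing is lost. Confidence is high on the text and the direction. The magnitude rests on assumed shares and on a simple model without a size term.

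The flaw should be corrected, but it does not invalidate the trial.

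**What to change.** Replace the covariate rule in section 8.1 with:

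*All models, including the primary comparison, include organization size, trial centre and the 2008-2009 rate as pre-specified covariates. No covariate is selected by a test of baseline difference.*

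Keep baseline comparisons descriptive, as the Statistical Methods section already has them. Reconcile Randomization Sequence Generation with Randomization Type, so that one allocation method is stated.

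The cost is one sentence and about two degrees of freedom beyond the size terms already planned. A two-arm comparison of 46 clusters has 44; size in three categories takes two, and centre and baseline rate take one each, leaving 40.

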1.2 Poor Uptake of Influenza Vaccine by Healthcare Personnel

Despite abundant evidence of the safety and efficacy of the influenza vaccine, immunization rates among healthcare personnel in hospital and long-term settings remain well below the public health target of 90%. Current initiatives targeted at increasing healthcare personnel immunization rates are having limited success with healthcare personnel immunization rates as low as 2%, but averaging 40% - 60% in most healthcare facilities being reported (1,2,12).

1.3 Development of the Guide: “Successful Influenza Immunization Campaigns for Healthcare Personnel - A Guide for Campaign Planners”

Healthcare organizations have a wide variety of approaches to the immunization of their workers. Each influenza season, healthcare planners devote time and effort to encourage staff immunization through a seasonal influenza immunization campaign. While the majority of healthcare organizations are committed to vaccinating their personnel, they, however, work in isolation, with few resources and limited evidence to inform the development and running of a successful immunization campaign. Moreover, there are almost no additional resources available and often few opportunities to share ideas, ask questions, or boast successes with other organizations (14).

During the first year of the project team’s grant (2008-2009), we conducted a series of consultation meetings in Ontario and Nova Scotia with five long-term care homes and three acute care hospitals. We spoke to the influenza campaign teams typically comprising of occupational health and infection control leaders as well as other managers. The results of these consultation meetings led to the first draft of the Guide: “Successful Influenza Immunization Campaigns for Healthcare Personnel: A Guide for Campaign Planners” (see Appendix 1).

The goal of this study is to validate the Guide and additional web-based “grab and go” tools (the Toolkit).

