**Intervention Group – March 2011 and March 2012**

- Immunization rate data for each year
- Campaign Details Questionnaire
- Assessment of the Guide
- Assessment of the revised OIDA
- Assessment of the Toolkit

All questionnaires will be given as self-administered questionnaires and will be available online or via email. Each questionnaire will include check-box questions (which will be analyzed using descriptive analysis) and open-ended questions. The results from the open-ended questions and information gathered from the workshops, webinars, and teleconferences, plus interactions with the research team throughout the campaign season, will be summarized and synthesized in a post-campaign report each year.

1. **Study Outcomes**
   1. Primary Outcome

In the Intervention Group, a 10% improvement in healthcare personnel immunization rates from the base year (2008-2009) as compared to Year One (2010-2011) and Year Two (2011-2012)

This will be assessed by conducting a time-series analysis on how each organization does against themselves and between the Intervention and Control Group. In our systematic review of the effectiveness of influenza campaigns in healthcare organizations published in the Canadian Medical Association Journal (15) (see Appendix 2), methods for calculating change scores were used that enable comparisons across different types of studies randomized trials with only “after” assessments in the intervention and control groups as well as comparisons of studies that had change scores based on before and after the campaigns in control and intervention groups.

Also, we will assess the immunization rates against the benchmark of 90% set by the National Advisory Committee on Immunization (17).

- 1. Secondary Outcome

In both the Intervention and Control Group, we will assess improvement in the reporting of immunization rates, based on the methodology outlined in Appendix 3 of the Guide (16).

- 1. Tertiary Outcomes

Improvement in how each organization plans, implements, monitors, and evaluates their campaign will be observed. We will track this improvement comparing their campaign activities each year against the benchmarks established by the Checklist in the Guide.

Overall satisfaction with the Guide and with the delivery methods of the Guide, including preferences for web-based or paper tools, ease of use, practicality of application, and the need for outsider intervention, will be assessed.

1. **Sample Size**

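### The protocol names two incompatible primary outcomes, change in immunization rate and attainment of 90%, and the trial is sized only for a comparison of rates

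*Protocol*

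**What the plan says.** **Study Outcomes, Primary Outcome.** The primary outcome is "In the Intervention Group, a 10% improvement in healthcare personnel immunization rates from the base year (2008-2009"), looking at Year One and Year Two. It is to be assessed by a "time-series analysis on how each organization does against themselves and between the Intervention and Control Group". The benchmark comes afterwards as an addition: "Also, we will assess the immunization rates against the benchmark of 90" per cent.

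**Statistical Methods, opening paragraph.** "The primary analysis will consist of comparing the Intervention Group with the Control Group".

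**Section 8.1, first paragraph.** For each of the two years, "we will use t-test to compare immunization rate difference means of the control group to the intervention group".

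**Section 8.1, second paragraph.** Linear models are assigned to improvement from the base year, and logistic models to attainment of 90%.

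**Section 8.1, third paragraph.** "While the primary outcome will be attainment of the recommended benchmark of 90% set by the National Advisory Committee on Immunization", followed by a repeated measures analysis over the three seasons.

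**Sample Size.** The trial is sized on a 20% difference between intervention and control organizations, with ICC 0.05, 150 personnel per organization, 46 organizations (23 allocated to intervention), 80% power and 5% significance. The control rate is not given, nor whether the 20% is absolute or relative.

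**Section 1.2.** Uptake is described as "averaging 40% - 60% in most healthcare facilities being reported", with rates as low as 2% also reported.

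**The concern.** One outcome is continuous (change in an organization's rate). The other is binary (whether the organization reaches 90%). They answer different questions, use different models and need very different sample sizes. Both are called primary, and no sentence puts one above the other. Naming the primary outcome is the protocol's own task, so an analysis plan would have to overrule one of the two statements.

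If the contradiction stays, the definition can be chosen after the rates are known, and an interim analysis is planned after Year One. If the third paragraph of Section 8.1 is followed literally, the primary test is one the trial was not designed to support.

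A lesser fault is that the Study Outcomes wording places the 10% improvement in the Intervention Group. Read alone, that could be met by a general rise in uptake between 2008-2009 and the later seasons, with no effect of the Guide.

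**Working it through.** **1. What the 46 organizations are sized for.** The design effect is 1 + (150 − 1) × 0.05 = 8.45. The Kelsey formula per arm is n = (1.96 + 0.84)² × 2 × p̄(1 − p̄) / d². A two-sided 5% level is assumed.

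- 20% read as relative to an assumed 50% control rate (50% vs 60%): n = 388.5. Then 388.5 × 8.45 / 150 = 21.9 organizations per arm, or 44 in total. With continuity correction n = 408, giving 22.98 per arm, or 46 in total.
- 45% vs 55%: n = 392.4, giving 22.1 per arm, which rounds up to 23, or 46 in total.
- 20% read as 20 percentage points (pairs from 30% vs 50% to 70% vs 90%): only 8 to 14 organizations in total.

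So 46 is reproduced by a between-arm comparison of immunization rates about 10 points apart. The 20-point reading does not give it, and no attainment proportion enters the calculation.

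**2. Power for the comparison of rates.** The variance of an organization's rate is p(1 − p) × 8.45 / 150. This gives an SD of 0.119 at 50% and 0.116 at 60%. The standard error of the difference is √[(0.119² + 0.116²)/23] = 0.0346, so 0.10/0.0346 = 2.89 and power is Φ(2.89 − 1.96), about 82%. For change scores the relevant SD is that of the change, which the protocol does not give. For a 10-point difference, power is 92% at an assumed SD of 0.10, 81% at 0.12, 62% at 0.15 and 40% at 0.20.

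**3. Power for 90% attainment.** Organization rates are assumed beta-distributed with mean μ, with parameters μ(1/ICC − 1) and (1 − μ)(1/ICC − 1). Attainment means at least 135 of 150 staff immunized (beta-binomial). Control rates of 50% and 60% come from the upper half of the range in Section 1.2, which favours attainment. The expected count is 23 × (sum of the two arms' probabilities). The chance that no control organization attains is (1 − control probability)²³. Power is for Fisher's exact test, 23 per arm, two-sided 5%.

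At ICC 0.05 the probability that one organization attains is 0.00005 at a mean of 50%, 0.0013 at 60%, 0.019 at 70% and 0.153 at 80%.

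| ICC | Control vs intervention | Expected at 90%, of 46 | No control organization at 90% | Power |
|---|---|---|---|---|
| 0.05 | 50% vs 60% | 0.03 | 99.9% | about 0% |
| 0.05 | 60% vs 70% | 0.46 | 97% | below 0.1% |
| 0.05 | 60% vs 80% | 3.5 | 97% | 26% |
| 0.10 | 50% vs 60% | 0.45 | 94% | about 0% |
| 0.10 | 60% vs 70% | 2.2 | 67% | 2% |
| 0.10 | 60% vs 80% | 6.5 | 67% | 63% |

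With 0 of 23 attaining in control, significance needs at least 5 of 23 in the intervention arm (P = 0.049; 4 of 23 gives P = 0.109). Power of 80% needs about 28% attainment against almost none, or about 41% against 5%.

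**4. The logistic model.** If one arm has no attaining organization, the ordinary odds ratio has no finite estimate. At ICC 0.05 the chance of at least one empty arm is 97% or more in all three scenarios.

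**5. Wider spread (assumed).** With a between-organization SD of 0.20 and a mean of 60%, 1.4 of 23 organizations would be expected at 90%. With an SD of 0.25 the figures are 3.1 of 23 at a mean of 60% and 6.7 of 23 at 70%.

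**The case against.** **Are there really three primary outcomes?** A reader might infer three: a within-arm gain, a between-arm difference and 90% attainment. The documents do not support that count. The sentence after the 10% improvement says it is assessed between the groups as well as within organizations, the first research objective concerns the two groups, and the primary analysis is between arms. The first two are one outcome, loosely worded, so it would also be wrong to say that the plan discards its randomized control. The words that confine the improvement to the Intervention Group still need to go.

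**Is 90% attainment impossible to estimate?** A reader might infer this from the table, but it goes too far. The protocol gives no distribution of organization rates, 0.05 is a planning value, and reported rates as low as 2% suggest that the spread may be wider. A few organizations per arm could then reach 90%, and the effect would be estimable but imprecise. Section 8.1 also promises to check model assumptions and adjust, but that is generic and does not restore power.

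**Does the time-series wording add another definition?** No. Section 8.1 describes a repeated measures analysis over three seasons, so the term is loose rather than a rival outcome.

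None of this removes the conflict between change in rate and attainment of 90%, or supplies a sentence that ranks them.

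**Conclusion.** The point stands as a two-way contradiction. Study Outcomes, the between-arm primary analysis and the t-test make change in rate from 2008-2009 primary, while a later sentence in Section 8.1 makes 90% attainment primary. It should be corrected before any outcome data are analysed.

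The trial is not sized for attainment. On the plan's ICC and cluster size, power is between about 0% and 26% for true differences of 10 to 20 points from a base of 50% or 60%, and the logistic model would very likely meet an empty arm. Doubling the ICC raises power to at most 63% in these scenarios. The comparison of rates has about 82% power for 50% vs 60%.

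These sizes rest on a two-sided 5% test, control rates taken from Section 1.2, beta-distributed organization rates and equal clusters of 150. The 82% refers to rates in a single season. Power for change depends on an SD that the protocol does not state. The contradiction itself rests on none of these assumptions.

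**What to change.** - In Study Outcomes and Section 8.1, state the same single primary outcome: the between-arm difference in change in organization immunization rate from 2008-2009.
- Delete the restriction to the Intervention Group, so that a secular rise cannot satisfy the outcome.
- State whether the 10% is absolute or relative, and reconcile it with the 20% under Sample Size, whose scale also needs stating.
- Name Year One or Year Two as primary. Section 8.1 now tests both, so one outcome would still give two primary tests.
- Replace the Section 8.1 sentence that calls 90% attainment primary. Make it a secondary outcome, reported as counts per arm with exact confidence intervals.
- For consistency, describe the three-season analysis as repeated measures in both places.

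This is a wording amendment and needs no extra data. It should be made before the Year One interim analysis. The cost is that the 90% benchmark loses primary status.
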